## Methods/design

### Study objectives and hypothesis

The primary objective of this study is to estimate the efficacy of SABR for primary RCC. The primary endpoint is freedom from local progression, as defined by lack of progression of the target lesion (primary RCC) as measured by RECIST criteria [66]. The primary hypothesis of this study is that freedom from local progression at 1-year post-treatment will be > 80%.

Key secondary endpoints include assessment of a) Toxicity, as measured by CTCAE v4.03; b) Overall survival; c) Cancer specific survival; d) Freedom from distant failure; e) Renal function measured by serum creatinine and estimated glomerular filtration rate (eGFR) using CKI-EPI equation, split function and calculated glomerular filtration rate (GFR) on nuclear medicine testing; f) Cost-effectiveness. An exploratory objective is to assess the utility of multi-parametric MRI (mpMRI) as a biomarker of treatment response in a subset of patients.

This trial will be conducted in radiation oncology treatment centres throughout Australia, the MAASTRO clinic in the Netherlands, and the Royal Marden Hospital in England. All participating centres must successfully complete pre-trial quality assurance procedures prior to enrolling patients to the study. This will consist of an initial credentialing phase involving phantom dosimetry audit, facility questionnaires and a plan quality benchmarking exercise. Real-time quality assurance through plan reviews will be performed as part of the trial.

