### Sample size and study duration

In total, 70 patients are required for this study. It is anticipated that it will take 36 months to complete target accrual. The sample size of 70 patients was chosen to provide sufficiently narrow confidence intervals for clinical outcomes. If up to 15% of participants do not proceed to treatment, or die or are lost to follow-up before experiencing a local progression in the first year, and assuming the freedom from local progression (FFLP) at 1-year is 90%, the corresponding two-sided 95% confidence interval will be 79–96%. A 1-year freedom from local progression of 80% or less will be considered undesirable and not worthy of proceeding to a future randomised study against other treatment modalities. The freedom from local progression at 1-year is expected to be around 90%. With those assumptions, the proposed sample size will have 80% power with 10% alpha to test the null hypothesis that the FFLP at 1-year is 80% or less. The study end date is deemed to be the date of last data capture, which will be when the final participant completes the 5 year follow-up visit. Participant assessments are tabulated in Table 2.

**Table 2 Tab2:** Participant Assessments

ASSESSMENTS	Pre-Registration^a,b^	Post Treatment^c^													Post Progression^f^
		4 wks	3 mths	6 mths	9 mths	12 mths	18 mths	24 mths	33 mths	42 mths	51 mths	60 mths	Annually thereafter^d^	Progression^e^	Annually
Informed Consent	✓														
Informed consent for Health Economics data^g^	✓														
CT (Thorax/Abdomen)	✓^h,i^			✓	✓	✓	✓	✓	✓	✓	✓	✓	✓	✓^h,i^	
Split Renal Function Test (DMSA SPECT/CT) and calculated GFR (Cr-51 EDTA) ^j^	✓					✓		✓		✓		✓	✓^j^		
Whole body bone scan	✓													✓	
Clinical Consultation	✓		✓	✓	✓	✓	✓	✓	✓	✓	✓	✓	✓	✓	
Eligibility confirmation	✓														
Blood Tests^k^ and eGFR ^l^	✓	✓	✓	✓	✓	✓	✓	✓	✓	✓	✓	✓	✓	✓	
QLQ-C30 questionnaire ^m^	✓	✓	✓	✓	✓	✓	✓	✓	✓	✓	✓	✓			✓^m^
Adverse Event Reporting	✓	✓	✓	✓	✓	✓	✓	✓	✓	✓	✓	✓	✓	✓	
Survival Status															✓
MRI Sub study^n^															
Informed Consent	✓														
Multiparametric MRI	✓		✓			✓									

^a^To be done within 8 weeks of registration

^b^Treatment to commence within 6 weeks of registration

^c^Calculated from the date of the last radiotherapy fraction given. Post treatment follow-up to continue until both local and distant progression has been recorded

^d^After participant has both local and distant progression documented, annual survival status will be collected

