### Imaging sub-study 1: Evaluation of renal function change in response to SABR

Preservation of renal function is a major objective of kidney SABR. We will obtain split function nuclear medicine studies at baseline and 12, 24, 42 and 60 months after SABR for each patient enrolled in this trial. We will use deformable image registration to register the CT component of each DMSA SPECT/CT with the treatment planning CT, and apply this registration to the SPECT data. This will result in a 3D map of the DSMA uptake in the same spatial frame of reference as the planned radiotherapy dose. Based on this, we will then determine the change in DSMA uptake with radiation dose, and link any change as observed on imaging with clinical toxicity. Understanding the renal toxicity dose response will inform dose constraints on future patients. This information can further be used to optimise treatment plan quality in future renal SABR patients to minimise the dose to the functional components of the kidney.

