### Statistical considerations

Baseline characteristics will be summarised using descriptive statistics including counts and percentages for categorical variables and mean, standard deviation (SD), median and range for continuous variables. The Kaplan-Meier method will be used to estimate the OS, FFLP and freedom from distant progression. Annual estimates will be provided alongside 95% CI. An exploratory analysis will be carried out assessing the impact of baseline and treatment characteristic on OS using a Cox proportional hazard model. Cumulative incidence curves for cancer related death will be provided assuming competing risks with non-cancer related death as a competing event. Cumulative incidence curve for Grade 3+ toxicity will be provided assuming competing risks with death not related to treatment considered as a competing risk. A table with the frequency of worst AE grade experienced will also be provided for each individual AE type.

Change over time in renal function (serum creatinine, eGFR using CKI-EPI equation, split renal function and calculated GFR using nuclear medicine assessments) will be described using linear mixed models. The linear mixed model will include time as fixed effect (as a factor) and patients as a random effect. Mean and 95% confidence intervals will be calculated for each time point and the data will be displayed graphically using contrast from the linear mixed models. Changes from baseline will also be estimated using contrast from the linear mixed model. The impact of medical factors on renal function decline will be assessed by including relevant variables as independent variables in the linear mixed model.

No imputation of missing values and no adjustments for multiplicity are intended. This trial aims to a) describe clinical outcomes of patients with RCC treated with SABR and b) assess whether it is worthwhile conducting a future large randomised trial against other treatment modalities. The descriptive part of the study will use 5% alpha to provide two-sided 95% confidence intervals for clinical outcomes while the hypothesis testing on the FFLP at 1 year will use a one sided test with 10% alpha.

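### The plan assesses factors for renal function decline through a model term that, read in the ordinary way, measures average level rather than change

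*Protocol article*

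**What the plan says.** Everything on this point is in the protocol article, section Statistical considerations, apart from the objective and the visit schedule.

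- Outcomes: "Change over time in renal function (serum creatinine, eGFR using CKI-EPI equation, split renal function and calculated GFR using nuclear medicine assessments) will be described". Each is to be fitted with a mixed model, so the outcome is a measured level at each visit.
- Structure: "The linear mixed model will include time as fixed effect (as a factor) and patients as a random effect".
- Change: "Changes from baseline will also be estimated using contrast from the linear mixed model". A contrast with baseline is possible only if the baseline visit is one of the time levels, so baseline values are part of the outcome.
- Factors: "The impact of medical factors on renal function decline will be assessed by including relevant variables as independent variables in the linear mixed model".

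No factor-by-time interaction, factor-specific slope or change-score outcome is mentioned there or elsewhere in the article. Renal function is a secondary endpoint (Study objectives and hypothesis), and Imaging sub-study 1 states that "Preservation of renal function is a major objective of kidney SABR".

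**The concern.** The question asked is about decline, which is change over time. The method given, read in the ordinary way, answers a question about level. These differ whenever a factor is related to renal function before treatment. In this trial that is likely: the exclusion criteria rule out only an eGFR below 30, and many patients will be medically inoperable, so baseline function should vary widely and follow comorbidity.

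Two errors can follow. A factor that goes with poor kidneys at entry, but does not alter their course after SABR, can be reported as affecting decline. A factor that does alter the course can be missed, most easily if the affected patients start with better function.

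**Working it through.** **1. What the coefficient estimates (no assumed values).** With factor x added, the model is E[Y at time t] = μ_t + βx. The change from baseline is (μ_t + βx) − (μ_0 + βx) = μ_t − μ_0 for every x, so β says nothing about differential decline.

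Suppose the truth is a baseline difference α and an extra loss of δ per year: E[Y] = μ_t + αx − δxt. With complete data the estimate of β is the difference between groups in patients' averages over visits, with expectation α − δ·t̄, where t̄ is the mean visit time. The baseline gap enters in full. Decline enters only through t̄, and the two can cancel.

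As an illustration, one simulated data set had true 60-month declines that differed by 10 units. The fit without interaction gave both groups a change of −20.3. The fit with interaction gave −17.0 and −23.6.

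**2. Inputs for size.** The plan gives no figure for this analysis, so there is none to reproduce.

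- From the documents: 70 patients with up to 15% lost in the first year, 70 × 0.85 = 59.5, taken as 60. Blood tests (Table 2) at baseline, 4 weeks and 3, 6, 9, 12, 18, 24, 33, 42, 51 and 60 months: 12 visits, t̄ = 1.80 years, S = Σ(t − t̄)² = 32.2.
- Assumed: a binary factor split 30/30, between-patient SD 15, slope SD 2 per year, residual SD 6 (mL/min), complete follow-up, two-sided 5% tests.

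**3. Test on the added covariate.** SD of a patient's average = √(15² + (2 × 1.80)² + 6²/12) = √(225 + 12.9 + 3) = 15.5. Standard error of the difference = 15.5 × √(2/30) = 4.01.

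**4. Test on slopes.** SD of a patient's fitted slope = √(2² + 36/32.2) = 2.26. Standard error = 2.26 × √(2/30) = 0.584. For δ = 2, 2/0.584 = 3.42.

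| Truth | Expected difference in averages | Added covariate significant | Slope test significant |
|---|---|---|---|
| Baseline 10 lower, same decline | −10 | 68–70% | 5% |
| Baseline 15 lower, same decline | −15 | 96% | 5% |
| Same baseline, 2/year faster decline | −2 × 1.80 = −3.6 | 14–15% | 92% |
| Baseline 5 higher, 2/year faster decline | 5 − 3.6 = +1.4 | 6–7% | 92% |

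The t-test calculation and repeated simulation (3,000 to 4,000 trials per row) agree. With no effect at all, both tests reject in about 5%.

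**5. Other assumptions.**

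- Between-patient SD 20: false attribution is 45% (gap of 10) and 80% (gap of 15).
- Five nuclear-medicine visits (0, 12, 24, 42, 60 months), other assumptions as above: 67% false attribution for a gap of 10; a true 2/year difference is found in 19% against 85%.
- The same five visits, 70 patients, between-patient SD 18 and no slope variation: 60% and 92% false attribution; detection 18% against 99.7% with the interaction. Here t̄ = 2.3, so −2 × 2.3 = −4.6 of the 10-unit difference at 60 months reaches the coefficient.

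**6. Would a simple repair work?**

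- *Factor by linear time, patient random intercept only.* The slope variation is absorbed into the residual variance: (11 × 36 + 4 × 32.2)/11 = 47.7. The model takes the SD of a slope as √(47.7/32.2) = 1.22, when it is 2.26. The nominal 1.96 limit is really 1.96 × 1.22/2.26 ≈ 1.05 standard errors, so the test rejects in about 29% of trials with identical decline. Simulation gives about 30%.
- *Post-baseline mean adjusted for observed baseline.* Observed baseline contains residual variation, so the adjustment slope is 225/(225 + 36) = 0.86, and 10 × 0.14 = 1.4 of a 10-unit gap remains. Simulated false positives are about 11% for a gap of 10 and 16–18% for 15. Power for a true 2/year difference is 54–57%, against 92%.

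**The case against.** The strongest reply is that the sentence does not say main effects only. A factor-by-time term is also an independent variable in the model, and the sentence names decline as its target. The article condenses a fuller protocol, and an analysis plan may list the exact terms. This stands in part: the text does not exclude an interaction. It does, however, state a method for a named question, and an analyst following it in the ordinary way would add covariates. That makes it more than detail left to another document.

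A reader might go further and infer that the reported risk factors will be wrong. The documents do not support that. The added covariate validly estimates a level difference, picks up part of a differential decline, and may belong to a factor that affects both. The risk is of factors mislabelled or missed.

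A reader might also link this to the remark in Imaging sub-study 1 about dose constraints for future patients. That remark belongs to a separate dose-response analysis, which already works with change in uptake. Nor does the article say which medical factors it means.

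Finally, the plan attaches formal testing only to the primary endpoint and treats the rest as descriptive. This limits the consequence, but an interval for a level difference presented as an effect on decline misleads in the same way as a p-value.

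**Conclusion.** The point holds as a mismatch between the question and the stated method. On the ordinary reading the factor's coefficient is an average level difference, baseline included, and the model allows no difference in decline. That conclusion is algebraic and needs no assumed values.

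The size does need them. Across the settings tried, false attribution runs from 45% to 96% for baseline gaps of 10 to 15 mL/min, and a true 2 mL/min/year difference is found in 14% to 19% of trials, against 85% or more with a test aimed at change. The percentages rest on assumed SDs, effects and an even split. They also assume complete follow-up to 60 months, which makes the power figures a best case in this population.

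Only a covariate analysis of a secondary endpoint is affected. The primary endpoint, the sample size and the unadjusted contrasts from baseline stand. Severity is moderate.

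**What to change.** Replace the sentence on medical factors with wording such as:

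*The impact of a factor on renal function decline will be assessed by its interaction with time, reported as between-group differences in change from baseline at the scheduled visits. If time is entered as linear for this purpose, the model will include a patient-level random slope as well as a random intercept; if time stays a factor, the within-patient covariance will allow for varying slopes. Inference on decline will not rest on the factor's main effect.*

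The covariance clause is needed because an interaction tested with a random intercept alone can be badly liberal (step 6 of the working). With 12 blood-test visits an unstructured covariance has 12 × 13/2 = 78 parameters, so a random slope is the more economical choice for those outcomes. Post-baseline means adjusted for baseline should not be offered as an equivalent.

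The cost is one sentence of analysis wording and a slightly larger model. No new data, visits or patients are needed. If the full protocol or analysis plan already specifies the interaction, the article's sentence need only be aligned with it.

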## Discussion

There is growing evidence to support the safety of SABR/SRS, its effect on local control and possible impact on overall survival for primary RCC. FASTRACK II is a study that will provide multicentre validation of the efficacy of SABR, which has previously only been demonstrated in single institutional and retrospective reports. At the time of writing, the study is open at eight sites across Australia and is actively recruiting, with two international sites in the process of activation. TROG 15.03 FASTRACK II will provide robust data on the efficacy of SABR for primary RCC in inoperable patients, to enable future larger phase III clinical trials.

## Abbreviations

4D: Four-dimensional
BED: Biological effective dose
CBCT: Cone beam CT
CT: Computerised tomography
CTCAE: Common terminology criteria for adverse events
DCE: Dynamic enhanced contrast
DMax: Peak dose
DWI: Diffusion weighted imaging
ECOG: Eastern co-operative oncology group
eGFR: Estimated glomerular filtration rate
FBE: Full blood count
HREC: Human research ethics committee
HRQOL: Health-related quality of life
ITV: Internal target volume
MRI: Magnetic resonance imaging
OAR: Organ at Risk
QA: Quality assurance
QALY: Quality-adjusted life year
RCC: Renal cell carcinoma
RFA: Radiofrequency ablation
SABR: Stereotactic ablative body radiotherapy
SRS: Stereotactic body radiosurgery
TCC: Transitional cell carcinoma
TROG: Trans tasman radiation oncology group
UEC’s: Serum urea and electrolytes
